The plan is to enroll 200 employees in total, with 100 participants in each group. In each of the four intake periods, we plan to include 24 to 26 participants, and will actively recruit to ensure sufficient numbers prior to randomization. Following randomization, an intent-to-treat analysis will be incorporated, including all study participants. Quantitative precision estimates suggest that this sample size is sufficient to detect any real and important benefit of CBE over literacy training on change in help-seeking behavior. Two RCT evaluations of MHFA (literacy) interventions among Australian healthcare workers found that 50% to 75% of workers reportedly offered help to a person with mental health problems, prior to the intervention [24,25]. Based on this, we expect an average of about 1–2 behaviors at baseline across the samples. To simplify, we approximate the precision to detect change in mean count from baseline to the 6 month follow-up using calculations for the linear mixed-effects model, but allowing for non-constant variance of the counts by assuming that the variance averaged over groups and occasions might be as high as 4. Also assuming high consistency of help-seeking within groups (test-retest correlation, 0.80), we have an 80% chance of finding a significant (p < .05) difference between the two groups in average change over 6 months of as little as 0.44 behaviors. That is, even if the real advantage of CBE over MHFA is very small (less than 1 new behavior, on average), we have a high probability of detecting it. The precision for estimating mediators such as changes in stigma scores is similarly high. Based on initial pilot data, there were significant increases in behavior over time therefore the projected sample size should be more than sufficient to detect change.

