The survey will include 6 main sections. Content and data collection methods will be identical in the two groups:**Demographic data** (gender, age, education, ethnicity, job tenure, position) will be gathered to obtain a basic profile of participants.**Mental health experience** – Participants will be asked whether they have a history of mental health issues, either in themselves or a family member (yes/no), the nature of these issues (examples provided), and any personal experiences with mental health issues over the past six months (yes/no). The presence of mental health issues is based on self report, and will be defined as changes in thinking, mood or behavior that impair day-to-day functioning [34]. This lay definition and examples will be provided to capture a range of experiences that may or may not have been formally diagnosed by a medical practitioner.**Help-seeking behavior** – Participants will be asked to report whether they accessed any services from a list of 10 health, workplace and community service options. Questions regarding service utilization are adapted from the 2012/2012 Canadian Community Health survey [36], in order to provide a population reference, although several work-related services (e.g. EAP, union) are added as an option. Participants may endorse more than one of the behaviors, and a summative score of the number of behaviors will be used to measure change in help-seeking. Since the incidence of reported help seeking may be low over the time frame of the study, attitudes or intent to seek help will also be tracked. Intention to seek psychiatric help is a significant predictor of behavior [18]. The Attitudes Toward Seeking Professional Psychological Help Scale–short form (ATSPPHS), a 10 question survey using a four point Likert-type scale response will be used to track beliefs and intent to seek professional help [37]. It is a widely used scale with good internal consistency (α = .78), and criterion validity supported by links between scale scores and mental healthcare use [37].**Outreach behavior** – Baseline and follow-up data will be gathered regarding personal contact with a co-worker about mental health problems (yes/no), and any contact over the past 6 months (yes/no). If contact did occur, participants will be asked whether they provided help to the co-worker, and if so, to identify the type of help from a list of 10 possible options. The list of “outreach” behaviors was based on the ones used for evaluation of the MHFA program (e.g. ‘spent time listening to problem’, ‘recommend professional help’) [34], with an adaptation to include a several work-specific options (e.g., ‘recommend EAP’, ‘offered assistance with job duties’). Participants are invited to check all behaviors that apply (with an open-ended option), and scoring is based on one point per action, with a summative score used to track change. In addition to the behavior list, participants will be asked to rate their confidence in providing help on a 7-point Likert scale.**Stigma towards co-workers with mental illness** – The MHCC Opening Minds Scale for Healthcare Providers will be used; a 20-item questionnaire that was designed to evaluate the attitudes of healthcare providers towards people with mental illness [38]. The tool has good internal consistency (α = .82), and satisfactory test-retest reliability (ICC = .66), with limited impact of social desirability [38]. This tool is being implemented in sites across the country by researchers with the Mental Health Commission Opening Minds team; therefore data from this project can be linked with the larger database.**Mental Health literacy** – Four vignettes of employees with workplace mental health issues will be used to assess awareness of issues and when/how to respond to these issues in the workplace. The vignettes are adapted for a healthcare workplace based on a review of vignettes reported in the literature study [33,39,40], as well as analysis of key issues reported in the pilot phase of the study. Vignettes will incorporate differences in gender, nature and severity of illness, and a 7-point Likert scale from novice to expert will be used to track key dimensions of literacy, including perceived knowledge about the condition, what to say/do and what resources to access [33].

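### Precision for stigma change is said to match that for the behavior count, but the only stability figure given for the stigma scale (ICC .66) does not support this

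*Protocol article*

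**What the plan says.** The precision argument stands in the Participants section of the Protocol article. For 100 employees per arm it takes a variance of 4 for the behavior count and a high within-person consistency of help-seeking ("test-retest correlation, 0.80"). From these it concludes that 80% power is available for a between-group difference in "average change over 6 months of as little as 0.44 behaviors". It then extends the conclusion to the mediators in one sentence: "The precision for estimating mediators such as changes in stigma scores is similarly high". No stigma SD, target difference or correlation accompanies that sentence.

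The Data collection section describes the stigma scale and reports "satisfactory test-retest reliability (ICC = .66". It does not give the retest interval or the population behind that figure.

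The Data analysis section, on Research Question 2, starts the mediation work with linear regressions of change in literacy and in stigma on intervention. Later steps follow only if associations appear.

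**The concern.** The precision of a change score depends directly on how strongly baseline and follow-up correlate. The behavior calculation gains much of its precision from a correlation of 0.80. The one figure the article offers on the stability of the stigma scale is clearly lower, so a reader has no ground in the document for expecting comparable precision for stigma change.

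Stigma is the mechanism on which the case for contact-based education rests, and its effect is a named part of Research Question 2. The between-arm comparison of stigma change is the gateway to the rest of that mediation path. A team that believes precision there is as good as for the behavior count may put more weight on a small or non-significant stigma difference than the design can bear.

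**Working it through.** **Inputs**
- Sample size: "The plan is to enroll 200 employees in total, with 100 participants in each group" (Participants).
- Level and power: "we have an 80% chance of finding a significant (p < .05) difference" (Participants). Sidedness is not stated; two-sided is assumed unless noted.
- Behavior variance 4, so SD 2: "assuming that the variance averaged over groups and occasions might be as high as 4" (Participants).
- Correlation r: 0.80, assumed for help-seeking (Participants); .66, the ICC of the stigma scale (Data collection), used here as a stand-in for the trial's correlation.
- Dropout: none, since the article expects little and states no inflation.
- Stigma SD and target difference: not given, so stigma results are in SD units only.

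**Formula**

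Detectable difference = (1.960 + 0.842) × sqrt(2V/100) = 2.802 × sqrt(2V/100). V is the per-person variance of the quantity compared, with equal SD at each survey and the same r between any two surveys. In SD units:
- 6-month score minus baseline: V = 2(1 − r)
- mean of the two follow-ups minus baseline: V = 1.5(1 − r)
- 6-month score adjusted for baseline: V = 1 − r²
- mean of the two follow-ups adjusted for baseline: V = (1 + r)/2 − r²

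**Step 1: the plan's own 0.44 behaviors**
- Mean of follow-ups minus baseline, two-sided: V = 4 × 1.5 × 0.20 = 1.2; 2.802 × sqrt(0.024) = 0.434. Power at 0.44 is 81%.
- 6-month change, one-sided: V = 4 × 2 × 0.20 = 1.6; (1.645 + 0.842) × sqrt(0.032) = 0.445. Power at 0.44 is 79%.
- 6-month change, two-sided: 2.802 × sqrt(0.032) = 0.501. Power at 0.44 is 69%, so this version does not reproduce the figure.

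The stated 0.44 is therefore reproducible from the plan's inputs. The article does not say which version was used, so all the analyses are carried forward.

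**Step 2: the same formulas in SD units, r = 0.80 against r = .66 (two-sided)**

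| Analysis | V at 0.80 | V at .66 | Detectable at 0.80 | Detectable at .66 | SE ratio |
|---|---|---|---|---|---|
| 6-month change | 0.40 | 0.68 | 0.251 | 0.327 | 1.30 |
| Mean of follow-ups minus baseline | 0.30 | 0.51 | 0.217 | 0.283 | 1.30 |
| 6-month, baseline-adjusted | 0.36 | 0.5644 | 0.238 | 0.298 | 1.25 |
| Mean of follow-ups, baseline-adjusted | 0.26 | 0.3944 | 0.202 | 0.249 | 1.23 |

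The ratio is sqrt(V at .66 / V at 0.80). For the two change scores it is sqrt(0.34/0.20) = 1.30.

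**Step 3: power at the difference that has 80% power under 0.80**

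Power = Φ(2.802/ratio − 1.960).
- Ratio 1.304: Φ(0.189) = 57%
- Ratio 1.252: Φ(0.278) = 61%
- Ratio 1.232: Φ(0.315) = 62%

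Equal standardized precision would need 100 × ratio² per arm: from 100 × 0.3944/0.26 = 152 to 100 × 0.34/0.20 = 170. This only expresses the size of the gap.

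**Step 4: power at a larger difference, 0.40 SD, with r = .66**
- 6-month change: 0.40/sqrt(0.0136) = 3.43; Φ(3.43 − 1.96) = 93%
- 6-month, baseline-adjusted: 0.40/sqrt(0.011288) = 3.76; Φ(3.76 − 1.96) = 96%

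**The case against.** The best defence is that the sentence is qualitative and that 0.80 was assumed for help-seeking only. The article never applies it to stigma, so there is no stigma calculation to be wrong. A detectable difference of 0.25-0.33 SD can still reasonably be called good precision, and power at 0.40 SD exceeds 90%. A condensed article may also leave calculations for secondary measures to the full protocol. All this stands, and it limits the point to an unsupported comparison. It does not rescue the comparison, because the article makes a positive claim and its only relevant figure points the other way.

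Four stronger readings are tempting and are not supported:
- A reader might infer that the two figures contradict each other. They describe different measures, and the claim contains no number.
- A reader might treat .66 as a favourable value, on the view that it is short-term reliability. The interval and population are not stated, so the trial's correlation could be lower or higher.
- A reader might take the plan's 0.44/2 = 0.22 SD, apply the two-sided 6-month change score at .66, and report 47% power. That formula gives only 69% for 0.22 SD at 0.80, so much of the fall from 80% comes from switching formula. With the mean of follow-ups minus baseline, which does reproduce 0.44, power for 0.22 SD goes from 81% to 59%.
- A reader might infer that the mediation analysis is weaker than stated, or that a null stigma result will be taken as no mediation. The article states no power for the mediation test, and nowhere says a null stigma result would be read that way.

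**Conclusion.** The claim of comparable precision is not supported for stigma. Taking the scale's ICC of .66 as the trial's correlation, the standard error of standardized change is 23% to 30% larger than at 0.80, with the detectable differences and power shown above.

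This rests on 100 analyzed per arm, a two-sided 5% test, equal SDs and correlations across surveys, independent participants, and .66 being a fair stand-in for the correlation over 3 to 6 months. The last of these cannot be checked from the article. Without a stigma SD or target difference, neither precision in scale points nor power for a relevant effect can be computed, so the document does not show that the trial is too small for its stigma question.

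The point covers stigma only. No stability figure is given for the literacy measure or for attitudes to professional help. It is a modest correction to a secondary question and leaves the primary outcome and the sample size as they are.

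**What to change.** 1. In the sample size justification, replace the sentence on mediators with the detectable stigma difference in SD units. For example: assuming a correlation of .66 between surveys, 100 per arm gives 80% power at two-sided 5% for a between-arm difference in stigma of about 0.25 to 0.33 SD, depending on the analysis. State the correlation as an assumption, give the range (0.20 to 0.25 SD if it were 0.80, larger differences if it is below .66), and add the stigma SD if one is available. This costs one or two sentences.

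2. In the first mediation step (Data analysis, Research Question 2), add the baseline stigma score as a covariate to the regression of stigma change. The intervention effect is then the same as from modeling follow-up stigma adjusted for baseline. At r = .66 the 6-month detectable difference falls from 0.327 to 0.298 SD. The baseline score is already collected, so this needs no extra data or participants. It does not touch the rule against added covariates, which concerns the primary analysis of the behavior count.

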### Interventions

The ***“Beyond Silence” CBE intervention*** program will be co-led by trained peer educators who have personally experienced mental ill health and recovery. The peer educators will be employees within the organization who not only have personal experience with mental ill health (either themselves or a close family member), but are good communicators and credible leaders within the organization. They will be recruited and trained to effectively teach the content, share their personal experiences, and facilitate discussion. Four employees (plus one “back-up” person) will contracted for approximately 125 hours over the course of the two years (including training and support sessions), with two peer educators facilitating each Beyond Silence group program. The Beyond Silence curriculum was designed to address the unique needs of the organization and is based on; a) pilot data from the initial qualitative phase of the project [33], b) a review of programs utilized in other workplaces, and c) best practice principles of contact based education and knowledge translation. It will include a series of 6 in-person group sessions (plus 5 online sessions) designed to provide information, diminish anxiety and promote empathy; all best-practice dimensions of CBE [28]. Sessions will be held weekly, alternating between a 1.5-2 hour in-person session and an online learning opportunity. The in-person sessions will combine information sharing and discussion, using workplace-based vignettes to build mental health literacy, reduce stigma and increase confidence and skill in reaching out to seek/offer help. The online “virtual” sessions using a secure, online platform, will encourage self-directed exploration of community and online resources and provide an opportunity for online dialogue that can be accessed at any time or place. All participants will receive a program handbook with the core content and worksheets. Each Beyond Silence program will be offered over a three month period. Over the course of the project, eight programs will be offered with approximately 12–13 participants per program.

The control group intervention is Mental Health First Aid (MHFA), a standardized, twelve-hour educational program designed to teach participants how to recognize the early warning signs of mental illness, how to provide initial help to someone in a mental health crisis, and how to support people who are developing mental health problems [25]. It is an evidence-based approach, with several RCT’s documenting significant increases in mental health literacy, decreased social distance, and increased reports of helping behaviors [24,34,35]. The program originated in Australia, but is being implemented across Canada, under the leadership of the Mental Health Commission of Canada. A staff member in each organization who has been trained through the 5-day instructor-training program will be seconded to facilitate the program within their organization. Each course will be offered as two full days, typically one week apart. All participants will receive a training manual, which covers all of the content of the standardized, module-based curriculum. Over the course of the project, eight courses will be offered with approximately 12–13 participants per course.

The location and specific dates/times for the sessions will be customized for each group in order to facilitate participation and maximize response rate, but groups will scheduled to start in regular intervals over the course of the two years (fall, winter, spring, fall). The Beyond Silence programs will be scheduled in the early evenings (outside of regular work hours), and the MHFA programs will be scheduled for two full days, one week apart.

Monthly meetings will be scheduled with the peer educators to provide support, address any questions/concerns, and maximize fidelity to the principles of the Beyond Silence program. A fidelity measure was designed to track adherence to structural elements (6 items), as well as content and process principles (10 items) of the program, using a 4-point Likert-type rating scale. Fidelity assessment will occur between sessions 3 and 5, and will be completed by a participant observer who is part of the core project team. Ratings will be discussed with peer educators at monthly meetings, with any departures from the established principles noted and explained, including plans (if applicable) to improve adherence. Fidelity to the MHFA program principles will be monitored through MHFA Canada, as per their internal processes.

### Data collection

Each participant will complete a survey prior to starting the training, immediately following the intervention, and three months following completion of the program. Participants will have the option of completing a written or online version of the survey that is sent directly to them by email and/or letter. Proactive outreach, with two follow-up reminders and a gift card incentive will be used to maximize return rates. Baseline data for the MHFA training will take place three months prior to initiation of the two-day program, so that the post-test measurements in the MHFA and Beyond Silence groups occur concurrently.

The survey will include 6 main sections. Content and data collection methods will be identical in the two groups:**Demographic data** (gender, age, education, ethnicity, job tenure, position) will be gathered to obtain a basic profile of participants.**Mental health experience** – Participants will be asked whether they have a history of mental health issues, either in themselves or a family member (yes/no), the nature of these issues (examples provided), and any personal experiences with mental health issues over the past six months (yes/no). The presence of mental health issues is based on self report, and will be defined as changes in thinking, mood or behavior that impair day-to-day functioning [34]. This lay definition and examples will be provided to capture a range of experiences that may or may not have been formally diagnosed by a medical practitioner.**Help-seeking behavior** – Participants will be asked to report whether they accessed any services from a list of 10 health, workplace and community service options. Questions regarding service utilization are adapted from the 2012/2012 Canadian Community Health survey [36], in order to provide a population reference, although several work-related services (e.g. EAP, union) are added as an option. Participants may endorse more than one of the behaviors, and a summative score of the number of behaviors will be used to measure change in help-seeking. Since the incidence of reported help seeking may be low over the time frame of the study, attitudes or intent to seek help will also be tracked. Intention to seek psychiatric help is a significant predictor of behavior [18]. The Attitudes Toward Seeking Professional Psychological Help Scale–short form (ATSPPHS), a 10 question survey using a four point Likert-type scale response will be used to track beliefs and intent to seek professional help [37]. It is a widely used scale with good internal consistency (α = .78), and criterion validity supported by links between scale scores and mental healthcare use [37].**Outreach behavior** – Baseline and follow-up data will be gathered regarding personal contact with a co-worker about mental health problems (yes/no), and any contact over the past 6 months (yes/no). If contact did occur, participants will be asked whether they provided help to the co-worker, and if so, to identify the type of help from a list of 10 possible options. The list of “outreach” behaviors was based on the ones used for evaluation of the MHFA program (e.g. ‘spent time listening to problem’, ‘recommend professional help’) [34], with an adaptation to include a several work-specific options (e.g., ‘recommend EAP’, ‘offered assistance with job duties’). Participants are invited to check all behaviors that apply (with an open-ended option), and scoring is based on one point per action, with a summative score used to track change. In addition to the behavior list, participants will be asked to rate their confidence in providing help on a 7-point Likert scale.**Stigma towards co-workers with mental illness** – The MHCC Opening Minds Scale for Healthcare Providers will be used; a 20-item questionnaire that was designed to evaluate the attitudes of healthcare providers towards people with mental illness [38]. The tool has good internal consistency (α = .82), and satisfactory test-retest reliability (ICC = .66), with limited impact of social desirability [38]. This tool is being implemented in sites across the country by researchers with the Mental Health Commission Opening Minds team; therefore data from this project can be linked with the larger database.**Mental Health literacy** – Four vignettes of employees with workplace mental health issues will be used to assess awareness of issues and when/how to respond to these issues in the workplace. The vignettes are adapted for a healthcare workplace based on a review of vignettes reported in the literature study [33,39,40], as well as analysis of key issues reported in the pilot phase of the study. Vignettes will incorporate differences in gender, nature and severity of illness, and a 7-point Likert scale from novice to expert will be used to track key dimensions of literacy, including perceived knowledge about the condition, what to say/do and what resources to access [33].

In addition to quantitative outcome data, qualitative data will be collected to track program implementation. Attendance will be recorded at each session, in order to understand patterns of participation and potential dose–response impact. At the end of each group, all participants will be asked to provide written feedback (as part of the post-group survey) regarding their experience, including perceived strengths of the program and suggestions for improvement. Feedback will also be gathered from peer educators regarding the program and their experience as facilitators. In the monthly support meetings, the project coordinator will inquire about and document notes regarding issues raised by the peer educators. As outlined earlier, monthly supervision meetings will also be used as a way of tracking fidelity to the program principles.

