### Data analysis

In accordance with Research Question 1, we hypothesize that help-seeking behavior will increase from baseline to 3 and 6 months by a greater amount in the Beyond Silence group than in the MHFA control. The primary approach to this question is the repeated measures analysis of a checklist of desirable help seeking/help providing behaviors, obtained from the survey at each time point. Overall tests of the change across all three measurements are available from generalized linear mixed-effects analysis, assuming that the count (from 0 to 20 behaviors) is distributed as a Poisson variable. This is a standard approach that accounts for over-dispersion in the Poisson model arising from the repeated measurements, permits the inclusion of participants who have not completed all three assessments, and allows for flexible modeling of the change over time and the inclusion of any relevant covariates [41]. In the primary analysis, the statistical significance of treatment group in this model will be used to address the first research question. In view of the randomized design, the primary analysis will not include additional covariates, but the model will be used to explore modifying effects by including additional covariates (e.g. age, sex, prior experience with mental illness) and interactions between these covariates and treatment group. As a secondary outcome, we will analyze a scaled measure of behavioral intentions using similar linear mixed-effects analysis.

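### At the post survey, Beyond Silence participants have had about three months of gradual training in which to act and MHFA participants about one week, and the six-month outreach window carries this imbalance into the final survey

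*Protocol article*

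**What the plan says.** **Survey times.** Data collection sets three surveys: "Each participant will complete a survey prior to starting the training, immediately following the intervention, and three months following completion of the program". For the control arm it adds: "Baseline data for the MHFA training will take place three months prior to initiation of the two-day program". The reason given is to align the two arms by date: "so that the post-test measurements in the MHFA and Beyond Silence groups occur concurrently".

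**Programs.** Under Interventions: "Each Beyond Silence program will be offered over a three month period", with weekly activity alternating between in-person and online sessions. For MHFA: "Each course will be offered as two full days, typically one week apart".

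**Outcome.** Data collection scores help-seeking and outreach as the number of items ticked on two lists of 10. The outreach section asks about contact with a co-worker in the preceding six months. The article states no window for the help-seeking list.

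**Analysis.** Data analysis hypothesizes a greater increase with Beyond Silence from baseline to both 3 and 6 months. It then says: "Overall tests of the change across all three measurements are available from generalized linear mixed-effects analysis". Significance of treatment group in that model answers Research Question 1.

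**Sample size.** Under Participants the justification is worded for one interval: "we approximate the precision to detect change in mean count from baseline to the 6 month follow-up". It gives a detectable difference of 0.44 behaviors with 80% power.

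**The concern.** A count of behaviors performed needs time after training in which to accrue. The schedule aligns the post surveys by date, and in doing so places a three-month untrained wait inside the MHFA baseline-to-post interval. The same interval in the other arm is filled with training. The wait comes from the survey schedule; the MHFA course itself does not require it.

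The trial asks whether Beyond Silence is more effective than an established program. If a follow-up point that enters the primary model favors one arm through timing, a significant result could arise from equally effective programs. Randomization balances the participants but cannot correct an outcome schedule that gives the arms unequal trained time.

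**Working it through.** **1. Trained time inside each interval**

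| | Beyond Silence | MHFA |
|---|---|---|
| Baseline to post survey | about 3 months of gradual training | about 3 months of waiting, then about 1 week between course days |
| Post to final survey | 3 months after completion | 3 months after completion |
| Six-month window at final survey | program period plus 3 months after | waiting period plus 3 months after |

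One week is about 1/13 of three months. The arms are comparable only in the last three months.

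**2. The plan's own figure**

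Inputs from Participants: variance 4, correlation 0.80, 100 per arm, p < .05 (sidedness not stated), 80% power. Normal approximation: detectable difference = (z for alpha + z for power) × SD of contrast × √(2/100).

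- Baseline to 6 months: SD = √(2 × 4 × 0.20) = 1.265.
  - Two-sided: 2.802 × 1.265 × 0.1414 = 0.501. Power at 0.44 is 69%, and 130 per arm would be needed for 80%.
  - One-sided: 2.486 × 1.265 × 0.1414 = 0.445.
- Mean of the two follow-ups minus baseline: SD = √(4 × (0.90 + 1 − 1.60)) = 1.095.
  - Two-sided: 2.802 × 1.095 × 0.1414 = 0.434. Power at 0.44 is 81%.

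So 0.44 is reproduced either by averaging both follow-ups two-sided, or by the worded contrast one-sided. The worded contrast tested two-sided gives 0.50.

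**3. Illustration of the gap with equally effective programs**

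The document gives no effect size, so these inputs are assumptions, except the baseline of 1–2 behaviors (Participants):

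- the baseline count refers to six months, so the monthly rate is 1/6 to 2/6, midpoint 0.25;
- training raises that rate by a fraction x, of 0.5 or 1;
- Beyond Silence ramps up linearly over its three months, and the single MHFA week is neglected.

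Post survey, with a three- or six-month window: gap = 3 × rate × x ÷ 2.

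- Midpoint rate, x = 1: 3 × 0.25 ÷ 2 = 0.375.
- Lowest case (rate 1/6, x = 0.5): 0.125.
- Highest case (rate 2/6, x = 1): 0.50.

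Final survey, midpoint rate, x = 1:

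- Six-month window: Beyond Silence gains 0.375 + 0.75 = 1.125 and MHFA gains 0 + 0.75 = 0.75. The gap is again 0.375.
- Window limited to the three months since completion: 0.75 in each arm, gap 0.

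**4. Effect on a nominal 5% two-sided test (linear approximation, midpoint rate, x = 1)**

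- Two follow-ups averaged, final window clean: bias 0.375 ÷ 2 = 0.1875, standard error 1.095 × 0.1414 = 0.155, rejection probability about 23%. With x = 0.5 it is about 9%.
- Final survey alone, six-month window: bias 0.375, standard error 1.265 × 0.1414 = 0.179, rejection probability about 55%.
- Final survey alone, window since completion: 5%.

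These rates show direction and sensitivity. They are not estimates for this trial.

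**The case against.** **Schedule is openly part of the comparison.** Methods/Design says that content, schedule and format differ, and practice during a spaced program can count as part of that program. This stands for the length of Beyond Silence. It does not cover the MHFA wait, which the survey timing creates.

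**Time coding is open.** The article says overall tests are available and that change over time can be modeled flexibly. With linear time at 0, 3 and 6 months and complete data, a slope contrast on the linear scale gives the middle survey no weight. This stands: the article does not establish that the two follow-ups are averaged, so a reader should not infer a fixed bias of about 0.19, or some 40% of 0.44. However, a linear slope would not remove the imbalance inside a six-month window at the final survey.

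**The illustration is crude.** The instrument counts kinds of behavior ticked, and outreach items apply only if contact occurred. The count need not grow in proportion to time, and the doubled rate has no source in the document. This also stands.

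**Stronger readings.** A reader might infer that MHFA participants had no chance to act, or that the post survey is in effect a wait-list comparison. The documents do not go that far: MHFA participants have a full course day about a week before finishing, and Beyond Silence is delivered gradually. A reader might also infer that moving the primary test to the last survey is enough. The six-month outreach window shows that it is not.

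**Conclusion.** The point holds as a matter of direction. If training raises behavior, the post-survey behavior comparison favors Beyond Silence even when the programs are equally effective, and that survey is in the model and hypothesis for Research Question 1. The six-month outreach window extends the asymmetry to the final survey, because half of the MHFA window is untrained waiting.

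The size cannot be fixed from the document. It depends on the training effect, how soon it shows in behavior, and how time is coded. If training does not change behavior, there is no bias. The illustrative gap of 0.125 to 0.50 shows only that it could be of the same order as the 0.44 the trial is designed to detect.

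**What to change.** 1. Name the change from baseline to the final survey as the single primary behavior contrast, as the sample size wording already describes. All three surveys can stay in the model.
2. At the final survey, ask both arms about behavior in the three months since program completion, and use a baseline window of the same length. Step 1 alone leaves the asymmetry in place.
3. Report post-survey behavior as descriptive, stating the unequal time since training began.
4. Keep the post survey for literacy, stigma and attitudes, which can be measured immediately after training.
5. Restate the detectable difference as about 0.50 behaviors (two-sided 0.05, 80% power, variance 4, correlation 0.80, 100 per arm), with about 69% power at 0.44.

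**Cost.** One changed recall instruction, fewer behaviors captured in the shorter window, and the loss of precision in item 5. The variance and correlation are the plan's own assumptions and should be reconsidered for a three-month window.
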